### Treatment

Starting at the enrollment visit, all youth sign an informed consent, are prescribed cART, and clinically treated according to standard of care HIV-1 management as defined in DHHS guidelines [9]. Genotypic drug resistance testing is performed before initiation of ART to guide the selection of the regimen. Once results of drug resistance testing are available, the treatment regimen can be modified if warranted.

Our study recommends that physicians prescribe fixed-dose combination regimens, favoring once-daily integrase inhibitor–based regimens. Use of complex ART regimens with the inclusion of protease inhibitors may trigger gastrointestinal symptoms and potential loss of adherence by our adolescent or young adult study youth, whereas efficacy of integrase inhibitor (integrase strand transfer inhibitor; INSTI)–based ARTs is successful in suppressing virus more rapidly than non-INSTI- based therapy [37]. By recommending fixed-dose combination once-daily integrase inhibitor–based regimens, we can minimize pill burden and the possibility of ART side effects. We hope that doing so will promote ART adherence and patient satisfaction in a population that is generally not amenable to medication use nor has prior experience with daily medications.

The fixed-dose combination once-daily integrase inhibitor–based regimens recommended may include the single-tablet regimen elvitegravir 150 mg/cobicistat 150 mg/emtricitabine 200 mg/tenofovir alafenamide 10 mg (EVG/COBI/FTC/TAF; Genvoya Foster City, CA: Gilead Sciences, Inc; 2016) [38] or elvitegravir 150 mg/cobicistat 150 mg/emtricitabine 200 mg/tenofovir disoproxil 300 mg (EVG/COBI/FTC/ TDF; Stribild Foster City, CA: Gilead Sciences, Inc; 2016), depending on availability or other similar regimens. EVG/COBI/FTC/TAF has been approved by the US Food and Drug Administration in November 2015 [39] and is similar to the approved single-tablet regimen with TDF but uses the TAF formulation of tenofovir, which appears to have distinct safety advantages. There have been many clinical trials that have included EVG/COBI/FTC/TDF and EVG/COBI/FTC/TAF. One phase-2 study (GS-US-292-0102) treated youth with both regimens and found that, although both groups had increased viral suppression, 88.4% (99/112) of those treated with EVG/COBI/FTC/TAF had HIV-1 RNA less than 50 copies/mL at 48 weeks by snapshot analysis compared with 88% (51/58) in those given EVG/ COBI/FTC/TDF [40].

**Table 1 table1:** Acute, recent, and established HIV infection as per Fiebig staging.

Cohort^a^ and group		Fiebig stage	Estmated time from infection (days)	HIV-1 antibody diagnostic profile
**Acutely or recently infected (estimated N=36)**				
	1	1 or 2	0-20	Nonreactive HIV-1 antibody
	2	3 or 4	20-30	Reactive HIV-1 antibody; negative or indeterminate results on the Western blot
	3	5	30-90	Reactive HIV-1 antibody; positive Western blot without p31 band
**Control or established (estimated N=36)**				
	4	6	90+	Reactive HIV-1 antibody; positive Western blot with p31 band

^a^Adapted from: Fiebig et al study [11].

**Table 2 table2:** Schedule of evaluations.

Evaluation	Screen	Entry	Week(s)				Month(s)				
			1	2	4	8	4	8	12	18	24
Documentation of acute HIV	X	—^a^	—	—	—	—	—	—	—	—	—
Fiebig staging	—	X	—	—	—	—	—	—	—	—	—
Financial screening	—	X	—	—	—	—	—	—	—	—	—
History	—	X	—	—	—	—	—	—	—	—	—
Physical examination	—	X	X	X	X	X	X	X	X	X	X
Adherence assessment	—	—	X	—	X	—	X	X	X	X	X
Antiretroviral therapy (ART) initiated	—	X	—	—	—	—	—	—	—	—	—
HIV-1/2 enzyme immunoassay fourth generation assay	—	X	—	—	—	—	—	—	—	—	—
HIV-1 genotypic testing	—	X	—	—	—	—	—	—	—	—	—
Urine analysis	—	X	—	—	—	—	—	—	—	—	—
Complete blood count with differential and platelets	—	X	—	X	—	X	X	X	X	X	X
Liver function tests (AST^b^, ALT^c^, GGT^d^)	—	X	—	X	—	X	X	X	X	X	X
Renal function tests (blood urea nitrogen, creatine)	—	X	—	X	—	X	X	X	X	X	X
T cell subsets	—	X	—	X	—	X	X	X	X	X	X
HIV-1 RNA PCR^e^ quantitative	—	X	—	X	—	X	X	X	X	X	X
HIV-1 Western blot	—	X	—	—	X	X	—	X	X	X	X
Hepatitis B and C panel	—	X	—	—	—	—	—	—	—	—	—
Rapid plasma regain	—	X	—	—	—	—	—	—	—	—	—
Gonorrhea/chlamydia PCR of urine, oropharynx, and rectum	—	X	—	—	—	—	—	—	—	—	—
Cytomegalovirus PCR blood	X^f^	X^f^	X^f^	X^f^	X^f^	X^f^	X^f^	X^f^	X^f^	X^f^	X^f^
Pregnancy test	—	X^g^	X^g^	X^g^	X^g^	X^g^	X^g^	X^g^	X^g^	X^g^	X^g^
Reservoir study laboratories (mL)	—	30	10	10	10	10	30	10	30	10	30

^a^Not applicable.

^b^AST: aspartate aminotransferase.

^c^ALT: alanine aminotransferase.

^d^GGT: gamma-glutamyl transferase.

^e^PCR: polymerase chain reaction.

^f^If clinically suspected.

^g^Whenever pregnancy is suspected.

Other potent antiretroviral regimens may be prescribed by the physician based on availability, patient tolerability, and preference. Changes to antiretroviral regimens should be performed when necessary according to HIV management guidelines [41]. Patients who do not tolerate the ART regimens will be prescribed an alternative ART regimen as clinically indicated. The same will occur with subjects who do not achieve viral load remission, and they may be prescribed an alternative ART regimen as clinically indicated.

Youth will take study medications and come for follow-up visits with physicians at clinic sites for up to 24 months according to the schedule of evaluations (Table 2) for assessment of viral load and HIV reservoir assays, as well as monitoring of coinfections. In addition to the enrollment visit, there will be a total of 9 follow-up visits during which samples will be collected for clinical Laboratoriess and immune reservoir studies. Of the 10 visits, 8 are scheduled during the first 12 months of ART, with 2 subsequent visits performed at 18 and 24 months.

The HIV WB is a part of immune reservoir studies and does not need to be repeated if it shows a full profile Fiebig stage 6 until 1 year. If subjects cannot do both a 2-week and 4-week follow-up visit, it is acceptable to combine the 2 visits into 1 as long as all clinical laboratory assays specified for week 4 are taken. The window periods (not shown in table) are as follows: −7 days for screen; ±7 days for week 1; ±14 days for weeks 2 and 4; ±7 days for week 8; and ±14 days for 4, 8, 12, and 24 months. In the event of virologic failure (not shown in table), HIV-1 genotypic testing will be conducted. In the event of premature study or treatment discontinuation (not shown), our team will try to collect HIV-1 genotypic testing, T cell subsets, HIV RNA quantitative assay, and 30 mL for immune reservoir studies.

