A number of clinical laboratory assays are performed and include the following: (1) complete blood count with differential and platelets, (2) liver function tests (aspartate aminotransferase [AST], alanine aminotransferase [ALT], and gamma-glutamyl transferase [GGT]), renal function tests (blood urea nitrogen [BUN] and creatinine), (3) CMV PCR blood if clinically suspected, (4) urine analysis, (5) gonorrhoea/chlamydia PCR of urine (6) RPR, (7) Hepatitis A, B, and C panel, (8) HIV-1 genotypic testing, (9) T cell subsets, and (10) urine pregnancy test (if female) and TB-Gold quantiFERON testing. In addition to these clinical laboratory assays, 30 mL of whole blood is collected for immune reservoir studies. Pregnancy testing is also performed if applicable.

#### Study Visits Postantiretroviral Therapy Initiation: Day 7, Week 8

A physical examination is performed, and information regarding clinical signs, symptoms, and findings of acute HIV infection or side effects from medication are recorded. Viral load testing, complete blood count, and chemistries are performed. Adherence assessment is performed, and pregnancy testing performed if applicable. In addition, 10 mL of whole blood is collected for immune reservoir studies.

#### Study Visits Postantiretroviral Therapy Initiation: Weeks 2 and 4

A physical examination is performed, and information regarding clinical signs, symptoms, and findings of acute HIV infection or side effects from medication are recorded. Adherence is assessed, and the following clinical laboratory assays are performed: (1) complete blood count with differential and platelets, (2) liver function tests (AST, ALT, and GGT) and renal function tests (BUN and creatinine), (3) HIV-1 genotypic testing (if clinically indicated or detectable viremia), (4) T cell subsets, (5) HIV-1 RNA PCR quantitative, and (6) urine pregnancy test (if suspected). In addition to these clinical laboratory assays, 10 mL of whole blood is collected for immune reservoir studies. At week 4, an HIV-1 WB is performed unless previous results showed a full profile Fiebig stage 6 (in that case, HIV-1 WB will be conducted at the 1-year mark).

#### Study Visits Postantiretroviral Therapy Initiation: Months 4, 8, 12, 18, and 24

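### Table 2, the rule for combining the week 2 and week 4 visits, and the visit text disagree on early assays; followed with Table 2, a combined visit can leave no HIV RNA between entry and week 8

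*Protocol article*

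**What the plan says.** Three places in the protocol article govern the early visits.

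- **The combining rule** (Treatment section, text after Table 2). For participants who cannot attend both week 2 and week 4, "it is acceptable to combine the 2 visits into 1 as long as all clinical laboratory assays specified for week 4 are taken". The same section names Table 2 as the schedule by which viral load is assessed.
- **Table 2.** The columns are screen, entry, weeks 1, 2, 4 and 8, and months 4, 8, 12, 18 and 24. The viral load row reads "HIV-1 RNA PCR^e^ quantitative — X — X — X X X X X X": entry, week 2, week 8 and every monthly visit, with nothing at weeks 1 or 4. The blood count row has the same pattern ("Complete blood count with differential and platelets — X — X — X X X X X X"), as do the liver, renal and T cell rows. The Western blot row is different: "HIV-1 Western blot — X — — X X — X X X X", so it falls at week 4 and not at week 2.
- **The visit descriptions** (Evaluations and Activities). For day 7 and week 8: "Viral load testing, complete blood count, and chemistries are performed". Weeks 2 and 4 share a single list of clinical laboratory tests that includes blood count, liver and renal tests and "4) T cell subsets, (5) HIV-1 RNA PCR quantitative, and (6) urine pregnancy test (if suspected".

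Adherence is assessed at day 7 and at weeks 2, 4 and 8 in the visit descriptions, but only at weeks 1 and 4 among the early visits in Table 2.

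**The concern.** The combining rule protects only what is specified for week 4, and the article gives two different answers to what that is. Under Table 2, week 4 has an examination, an adherence assessment, a Western blot, 10 mL of reservoir blood and two tests done only on suspicion. HIV RNA is not among them, so a combined visit could satisfy the rule and yield no viral load.

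The Study Aims include a comparison of viral dynamics and viral decay, and Descriptive Statistics plans a mean and SD for the time to suppression of viremia in acute cases. Both depend on the first weeks after treatment starts. Without an RNA between entry and week 8, suppression in that period can only be placed somewhere in the interval from day 0 to about day 56. The reservoir blood does not fill the gap, because at follow-up it is described as being used for HIV DNA by digital droplet PCR.

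**Working it through.** **Step 1: is the table read correctly?** Seven rows of Table 2 (examination, adherence, blood count, T cell subsets, HIV RNA, Western blot, reservoir blood) were set against the 11 column headings. Each has exactly 11 cells. The visit text independently puts a Western blot at week 4, where Table 2 also marks it. A column shift is therefore not the explanation.

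**Step 2: table and text side by side.**

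| Item | Table 2 | Visit text |
|---|---|---|
| HIV RNA | weeks 2, 8 | day 7, weeks 2, 4, 8 |
| Blood count, chemistries | weeks 2, 8 | day 7, weeks 2, 4, 8 |
| T cell subsets at weeks 2 and 4 | week 2 only | both |
| Adherence | weeks 1, 4 | day 7, weeks 2, 4, 8 |

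**Step 3: HIV RNA days up to week 8 (nominal days).**

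| Reading | All visits made | Weeks 2 and 4 combined, week 4 assays only |
|---|---|---|
| Table 2 | 0, 14, 56 | 0, 56 |
| Visit text | 0, 7, 14, 28, 56 | 0, 7, 28, 56 (combined visit on day 28) |

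The week 8 window is ±7 days, so the second RNA in the Table 2 combined case falls on days 56 − 7 = 49 to 56 + 7 = 63. The longest nominal gap is 56 days. If the Table 2 RNA planned for week 2 were kept in the combined visit, the longest gap would be 56 − 14 = 42 days with that visit on day 14, or 28 days with it on day 28.

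**Step 4: size of the effect on time to suppression.** The article gives no suppression times and does not define the event day. Assume that the event day is the first visit with suppressed RNA, that suppression persists once reached, and that times T are exponential with median m. Compare the full Table 2 schedule with a combined visit that has no RNA. Only participants suppressed by day 14 are recorded differently, on day 56 instead of day 14, so

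mean shift = (56 − 14) × P(T ≤ 14) = 42 × (1 − 2^(−14/m)).

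| Assumed median m | P(T ≤ 14) | Mean shift |
|---|---|---|
| 14 days | 0.500 | 21.0 days |
| 28 days | 0.293 | 12.3 days |
| 56 days | 0.159 | 6.7 days |

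As P(T ≤ 14) approaches zero, so does the shift. It applies to a participant who combines visits under the Table 2 reading. The shift in a group mean is this figure times the share of the group that combines visits, which the documents do not give.

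**The case against.** The best defence is that the rule was written with the visit text in mind. It speaks of clinical laboratory assays, the term the visit text uses for its shared week 2 and week 4 list, and that list contains HIV RNA. The article also states that "The HIV WB is a part of immune reservoir studies", and the Western blot is deferred to one year once a full stage 6 profile is seen. Table 2 then arguably leaves no unconditional clinical laboratory assay at week 4, so the rule has little content under the table and real content under the text. Combining two visits may also mean doing the work of both, with the week 4 assays as a minimum. The windows allow this: week 2 covers days 0-28 and week 4 covers days 14-42. Nothing tells sites to omit week 2 assays.

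Much of this stands. A reader might infer that anyone who follows the rule has no viral load before week 8; the documents do not support that, because under the visit text RNA would be available at day 7 and at the combined visit. Nor do they support saying that the lost data track treatment adherence: the rule concerns ability to attend, and no passage links combining visits to adherence.

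The defence does not remove the conflict. The section that contains the rule names Table 2 as the schedule for viral load, and Table 2 has none at week 4. Nor is this detail left out by a condensed article: rule, table and text are all printed, and they differ.

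**Conclusion.** The point holds as an internal contradiction with a conditional consequence. Table 2 and the visit text disagree on HIV RNA, blood count and chemistries at weeks 1 and 4, on T cell subsets at week 4, and on adherence assessment at weeks 2 and 8. Because the combining rule rests on the week 4 list, following it with Table 2 can leave a nominal 56 days without an HIV RNA; following it with the visit text does not.

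The consequence is confined to early viral decay and time to suppression in participants who combine visits. On the assumptions in the working, the recorded suppression day of such a participant is later by about 7 to 21 days on average for medians from 56 down to 14 days, and hardly at all if suppression by day 14 is rare. These figures are illustrations and not estimates for the cohort. A reader might also infer a threat to the primary comparison, but that is cell-associated HIV DNA at 24 months (Immune Reservoir Studies), which is not directly affected.

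**What to change.** Reconcile Table 2, the combining rule and the two visit descriptions (day 7 and week 8; weeks 2 and 4) so that each visit has one assay list and one entry for adherence assessment. Have the combining rule state which of the outcome assays already planned for weeks 2 and 4 a combined visit must include, so that the planned early HIV RNA is not lost by default. Which schedule is right is for the sponsor to decide.

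The cost is a table and text correction and a clarification to sites. Keeping assays that are already planned adds no new ones. Early samples not drawn before the clarification cannot be recovered, and the article describes enrollment as ongoing.

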### Evaluations and Activities

#### Screening Visit: Day of Diagnosis

During screening, youth are asked a series of questions as part of protocol 147 procedures. If HIV diagnosis is confirmed, a baseline interview will be conducted or if previously completed in study 3, a completed assessment interview will be performed. If youth are referred from other health care providers, the baseline assessment occurs after enrollment into the acute infection Protocol 147 (Table 2).

#### Study Entry: Day 0

Although screening visit and day 0 may occur on the same day, subjects are enrolled within 48 to 72 hours of an HIV diagnosis, and every attempt is made for treatment initiation to happen on the day of the first study visit. On this day, any necessary confirmatory diagnostic testing is performed, and those who are eligible for the study will provide written informed consent for study participation. Behavioral interventions are provided, and demographic and medical histories are collected and recorded in case report forms. A physical examination is performed, and information regarding clinical signs, symptoms, findings of acute HIV infection, and clinical treatment initiation are recorded. Patients are prescribed antiretrovirals for treatment initiation at this first visit.

If youth newly identified with HIV infection report a partner with unknown or negative HIV serostatus, we invite the study participant to bring their partner to clinic for HIV voluntary testing and counseling and also for pre-exposure prophylaxis (PrEP) initiation as part of overall HIV prevention efforts. If partners are seronegative, they are prescribed PrEP and referred to another ATN companion study (ATN149), where high-risk HIV seronegative youth are followed over time.

A number of clinical laboratory assays are performed and include the following: (1) complete blood count with differential and platelets, (2) liver function tests (aspartate aminotransferase [AST], alanine aminotransferase [ALT], and gamma-glutamyl transferase [GGT]), renal function tests (blood urea nitrogen [BUN] and creatinine), (3) CMV PCR blood if clinically suspected, (4) urine analysis, (5) gonorrhoea/chlamydia PCR of urine (6) RPR, (7) Hepatitis A, B, and C panel, (8) HIV-1 genotypic testing, (9) T cell subsets, and (10) urine pregnancy test (if female) and TB-Gold quantiFERON testing. In addition to these clinical laboratory assays, 30 mL of whole blood is collected for immune reservoir studies. Pregnancy testing is also performed if applicable.

#### Study Visits Postantiretroviral Therapy Initiation: Day 7, Week 8

A physical examination is performed, and information regarding clinical signs, symptoms, and findings of acute HIV infection or side effects from medication are recorded. Viral load testing, complete blood count, and chemistries are performed. Adherence assessment is performed, and pregnancy testing performed if applicable. In addition, 10 mL of whole blood is collected for immune reservoir studies.

#### Study Visits Postantiretroviral Therapy Initiation: Weeks 2 and 4

A physical examination is performed, and information regarding clinical signs, symptoms, and findings of acute HIV infection or side effects from medication are recorded. Adherence is assessed, and the following clinical laboratory assays are performed: (1) complete blood count with differential and platelets, (2) liver function tests (AST, ALT, and GGT) and renal function tests (BUN and creatinine), (3) HIV-1 genotypic testing (if clinically indicated or detectable viremia), (4) T cell subsets, (5) HIV-1 RNA PCR quantitative, and (6) urine pregnancy test (if suspected). In addition to these clinical laboratory assays, 10 mL of whole blood is collected for immune reservoir studies. At week 4, an HIV-1 WB is performed unless previous results showed a full profile Fiebig stage 6 (in that case, HIV-1 WB will be conducted at the 1-year mark).

#### Study Visits Postantiretroviral Therapy Initiation: Months 4, 8, 12, 18, and 24

A physical examination is performed, and information regarding clinical signs, symptoms, and findings of acute HIV infection or side effects from medication are recorded. Adherence is assessed, and the following clinical laboratory assays are performed: (1) complete blood count with differential and platelets, (2) liver function tests (AST, ALT, and GGT) and renal function tests (BUN and creatinine), (3) HIV-1 genotypic testing (if clinically indicated or detectable viremia), (4) T cell subsets, (5) HIV-1 RNA PCR quantitative, and (6) urine pregnancy test (if suspected). In addition to these clinical laboratory assays, 30 mL of whole blood is collected for immune reservoir studies.

### Immune Reservoir Studies

At enrollment, collection of 30 mL of (pretreatment) whole blood is collected and used to determine Fiebig staging through the following tests: (1) HIV-1 POC antibody test (fourth generation assay), (2) HIV-1 WB, and (3) HIV-1 quantitative RNA PCR. In addition, digital droplet PCR to measure full-length and partial HIV combination DNA transcripts are performed at enrollment and for each of the 9 subsequent follow-up visits. These tests allow the evaluation of continued reservoir suppression and sustainability of antiretroviral effect while comparing HIV viral dynamics across subject groups. The total amount of blood to be obtained during each study visit should not exceed 30 mL for youth weighing <50 kg.

The primary study endpoint is 24 months following enrollment, when the amount of cell-associated HIV-1 DNA in 5 million total peripheral blood mononuclear cells (assayed by quantitative digital drop PCR) will be compared between individuals initiating ART at different Fiebig stages: 1/2 versus 3/4 versus 5 versus established infection (Fiebig 6 control arm). We will also have HIV reservoir studies assessed at 4, 8, 12, 18, and 24 months. These data will be important to assess for studies of reservoir decay as well if there is drop out or loss to follow-up or evidence of viral rebound.

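### The blood-draw schedule contradicts itself: the 30 mL per-visit cap for youth under 50 kg is used up by the reservoir draw alone at four visits, and Table 2 and the text disagree (10 v 30 mL) at months 8 and 18

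*Protocol article*

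**What the plan says.** Four places in the protocol article bear on this.

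- **The cap.** Immune Reservoir Studies: "The total amount of blood to be obtained during each study visit should not exceed 30 mL for youth weighing <50 kg". It covers all blood at the visit, not only research blood.
- **Table 2, Schedule of evaluations, last row.** Reservoir blood is 30 mL at entry; 10 mL at weeks 1, 2, 4 and 8; then 30, 10, 30, 10 and 30 mL at months 4, 8, 12, 18 and 24.
- **Study Entry: Day 0.** After a list of clinical assays: "In addition to these clinical laboratory assays, 30 mL of whole blood is collected for immune reservoir studies. Pregnancy testing is also performed if applicable".
- **The later visits.** Under the heading "Study Visits Postantiretroviral Therapy Initiation: Months 4, 8, 12, 18, and 24", one description serves all five visits. It lists blood count, liver and renal tests, T cell subsets and HIV RNA, and then states: "In addition to these clinical laboratory assays, 30 mL of whole blood is collected for immune reservoir studies".

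The descriptions of the week 1, 2, 4 and 8 visits give 10 mL, in agreement with Table 2.

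Immune Reservoir Studies places the primary endpoint at month 24 and describes the measure thus: "the amount of cell-associated HIV-1 DNA in 5 million total peripheral blood mononuclear cells (assayed by quantitative digital drop PCR) will be compared". The contrast is across Fiebig groups. Under Regression Analysis, a longitudinal logistic model is planned if the provirus data are mainly a matter of being below the detection limit or not, and a linear longitudinal model if the outcome is numerical.

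**The concern.** There are two separate conflicts.

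The first concerns participants under 50 kg. The reservoir draw equals the whole per-visit allowance at four visits at which clinical blood is also due. A site must either exceed a stated participant limit or cut a sample, and the article does not say which sample gives way. Month 24, the primary time point, is one of the four. Enrolment starts at age 12, so participants under 50 kg are foreseeable, although their share is not given.

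The second concerns everyone. A site reading Table 2 draws 10 mL at months 8 and 18, and a site reading the text draws 30 mL.

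The analytic stake is secondary. A smaller draw may mean fewer cells in the assay, and fewer cells raise the detection limit. If that varied by visit or by body weight, it could enter a model of detectable v undetectable HIV DNA.

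**Working it through.** **Step 1. Table against text, visit by visit (reservoir mL).**

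| Visit | Table 2 | Text | Room under 30 mL cap, Table 2 | Room, text |
|---|---|---|---|---|
| Entry | 30 | 30 | 0 | 0 |
| Weeks 1, 2, 4, 8 (each) | 10 | 10 | 20 | 20 |
| Month 4 | 30 | 30 | 0 | 0 |
| Month 8 | 10 | 30 | 20 | 0 |
| Month 12 | 30 | 30 | 0 | 0 |
| Month 18 | 10 | 30 | 20 | 0 |
| Month 24 | 30 | 30 | 0 | 0 |

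Table and text differ only at months 8 and 18.

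Totals per participant:
- Table 2: 30 + 4 × 10 + 30 + 10 + 30 + 10 + 30 = 180 mL.
- Text: 30 + 4 × 10 + 5 × 30 = 220 mL.
- Difference: 2 × (30 − 10) = 40 mL.

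**Step 2. Cap against total draw.** Cap minus reservoir draw is 30 − 30 = 0 mL at entry and months 4, 12 and 24, and also at months 8 and 18 if the text governs. Clinical blood at months 4 to 24 covers blood count, liver and renal tests, T cell subsets and HIV RNA. At entry it covers blood count, chemistries, T cell subsets, genotype, syphilis serology, hepatitis panel and QuantiFERON. HIV RNA is not counted as extra at entry, because Immune Reservoir Studies draws the antibody test, Western blot and quantitative RNA from the 30 mL.

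Clinical tube volumes are not given. Assuming 5 to 20 mL:
- A full visit totals 30 + 5 = 35 mL to 30 + 20 = 50 mL.
- Holding to the cap would leave 30 − 5 = 25 mL down to 30 − 20 = 10 mL for reservoir studies.

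**Step 3. Could the smaller volume still supply the stated assay input?** The endpoint specifies 5 million peripheral blood mononuclear cells (PBMC). Yield per mL is not given; assume 0.5 to 2 million.
- Volume needed: 5 / 2 = 2.5 mL to 5 / 0.5 = 10 mL.
- 10 mL yields 10 × 0.5 = 5 million to 10 × 2 = 20 million cells.
- 30 mL yields 30 × 0.5 = 15 million to 30 × 2 = 60 million cells.

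Over this range 10 mL supplies the 5 million cells. At the low end nothing is left for the other immune assays.

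**The case against.** The strongest defence of the cap is that it is an exception for light participants that overrides the general schedule, with tube allocation left to a full protocol or laboratory manual. That reading is natural, and a missing allocation rule would not by itself be a finding in a journal article. But the article prints both the limit and a schedule that exceeds it. Table 2 footnotes other rows and not this one, and nothing says that the reservoir draw is what shrinks. The conflict stands.

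For months 8 and 18 there is no comparable defence: two volumes are printed for the same visits.

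The objection is much stronger against the analytic consequence. A reader might infer that reservoir samples cannot be comparable, or that a three-fold difference in volume moves the detection limit by log10(3) = 0.48. The document does not support either inference:

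- The month-24 measure is defined on a fixed 5 million cells. With equal cell input, the volume drawn does not change the quantity estimated and the shift is zero. The 0.48 holds only if cells assayed rise in proportion to blood drawn, which is nowhere stated.
- Table and text agree on 30 mL at month 24.
- The logistic model on detectability is conditional; otherwise a linear model is used.
- Under Table 2 the alternating volumes apply to all Fiebig groups alike, and nothing in the document links body weight to Fiebig stage. No bias in the between-group comparison is shown.
- Under the cap, the reservoir draw falls to 10 mL only if clinical tubes take 20 mL.

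What remains of the analytic point is limited: the 5 million input is stated only for the month-24 endpoint, while droplet PCR is planned at enrolment and all nine follow-up visits.

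**Conclusion.** Both contradictions hold as written and rest on no outside assumption. For participants under 50 kg, the cap leaves 0 mL for clinical blood at entry and months 4, 12 and 24, so following the schedule breaks a stated participant limit. For all participants, Table 2 and the text differ by 20 mL at each of months 8 and 18, or 180 v 220 mL of reservoir blood over the study.

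Comparability across visits or by body weight may be affected if smaller draws lead to fewer cells assayed. That is a possibility, not a demonstrated effect: it depends on clinical tube volumes, cell yield and the share of participants under 50 kg, none of which the article gives. The correction is worth making for the participant limit and the schedule alone, even if the analytic consequence is set aside.

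**What to change.** 1. Reconcile the reservoir volumes at months 8 and 18 between Table 2 and the description of the month 4 to 24 visits.
2. Reconcile the cap for youth under 50 kg with the total scheduled draw, reservoir plus clinical, at each visit. Which volumes and which cap are retained is for the sponsor to decide.
3. Record the number of cells assayed for each reservoir sample. If the detectable/undetectable model is used, take that number as the denominator and to set the sample's detection limit.

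The cost is a correction to one table and the matching text, and one recorded field per sample.
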